# Achieving Self-Directed Integrated Cancer Aftercare (ASICA) in melanoma: protocol for a randomised patient-focused pilot trial of delivering the ASICA intervention as a means to earlier detection of recurrent and second primary melanoma

**DOI:** 10.1186/s13063-019-3453-x

**Published:** 2019-06-03

**Keywords:** Primary care, Melanoma, Cancer, Randomised controlled trial, Survivorship, Self-directed care, e-health, ASICA

## Abstract

**Background:**

Melanoma is common; 15,906 people in the UK were diagnosed with melanoma in 2015 and incidence has increased fivefold in 30 years. Melanoma affects old and young people, with poor prognosis once metastatic. UK guidelines recommend people treated for cutaneous melanoma receive extended outpatient, hospital follow up to detect recurrence or new primaries. Such follow up of the growing population of melanoma survivors is burdensome for both individuals and health services. Follow up is important since approximately 20% of patients with early-stage melanoma experience a recurrence and 4–8% develop a new primary; the risk of either is highest in the first 5 years. Achieving Self-directed Integrated Cancer Aftercare (ASICA) is a digital intervention to increase total-skin-self-examination (TSSE) by people treated for melanoma, with usual follow up.

**Methods:**

We aim to recruit 240 adults with a previous first-stage 0-2C primary cutaneous melanoma, from secondary care in North-East Scotland and the East of England. Participants will be randomised to receive the ASICA intervention (a tablet-based digital intervention to prompt and support TSSE) or control group (treatment as usual). Patient-reported and clinical data will be collected at baseline, including the modified Melanoma Worry Scale (MWS), the Hospital Anxiety and Depression Scale (HADs), the EuroQoL 5-dimension 5-level questionnaire (EQ-5D-5 L), and questions about TSSE practice, intentions, self-efficacy and planning. Participants will be followed up by postal questionnaire at 3, 6 and 12 months following randomization, along with a 12-month review of clinical data. The primary timepoint for outcome analyses will be12 months after randomisation.

**Discussion:**

If the ASICA intervention improves the practice of TSSE in those affected by melanoma, this may lead to improved psychological well-being and earlier detection of recurrent and new primary melanoma. This could impact both patients and National Health Service (NHS) resources. This study will determine if a full-scale randomised controlled trial can be undertaken in the UK NHS to provide the high-quality evidence needed to determine the effectiveness of the intervention. ASICA is a pilot study evaluating the effectiveness of the practice of digitally supported TSSE in those affected by melanoma.

**Trial registration:**

Clinical Trials.gov, NCT03328247. Registered on 1 November 2017.

**Electronic supplementary material:**

The online version of this article (10.1186/s13063-019-3453-x) contains supplementary material, which is available to authorized users.

## Background

Melanoma is common; 15,906 people in the UK were diagnosed with melanoma in 2015 and incidence has increased fivefold in 30 years [1]. Melanoma disproportionately affects younger people with poor prognosis once metastatic [2]. UK guidelines recommend people treated for cutaneous melanoma receive extended hospital follow up to detect recurrence or new primaries [3–5]. However, delivering melanoma follow up to the growing population of melanoma survivors is burdensome for both individuals and health services [6]. Follow up is important, nonetheless, since approximately 20% of patients with early-stage melanoma experience a recurrence and 4–8% develop a new primary, the risk of either is highest in the first 5 years [7–10]. Melanoma can recur locally, regionally or with distant metastases, and new primaries can occur anywhere [11].

It is important to detect new primary and recurrent melanoma as soon as possible. Successful treatment of recurrent melanoma with targeted and immunological treatments is leading to significant improvements in survival even in advanced melanoma [12]. Most recurrences and new primaries are detected by patients between scheduled follow-up visits [3–5]. Thus, guidelines recommend patients conduct monthly total skin self-examination (TSSE) during follow up. An American randomised trial showed that increasing the practice of TSSE in the short-term results in significantly more skin surgery (i.e. in greater detection and tackling of potential melanoma) in people with increased melanoma risk [13].

However, currently people treated for melanoma are possibly missing opportunities for early detection of new primary and recurrent melanoma by not practising regular TSSE or not conducting it effectively. A Scottish study suggests that people delay raising concerns about early recurrence until their next hospital follow-up appointment [14]. There is also evidence from the UK and elsewhere that the practice of TSSE is suboptimal and not practised monthly as recommended by UK guidelines [3–5, 15, 16]. Barriers to initiating and maintaining TSSE include lack of initial training, declining motivation and insufficient time [17]. All of these barriers are tackled by the Achieving Self-directed Integrated Cancer Aftercare (ASICA) intervention.

The ASICA digital intervention supports high-quality TSSE by people with cutaneous melanoma, and appropriate clinical responses when they raise a concern. It is rigorously developed, digitally supported and theoretically based, using specified behaviour-change techniques to prompt users to perform regular TSSE. As reported in more detail elsewhere [18], the intervention was designed to incorporate specific “behaviour change techniques” or BCTs (i.e. the active ingredients that make up an intervention and are required to change behaviour). The BCTs included aimed to develop users’ knowledge and skills about TSSE (e.g. demonstrating the behaviour, rehearsing/practising); enhance/maintain motivation to perform TSSE (e.g. providing information on health consequences of the behaviour, using a credible source for the information); enhance confidence to conduct TSSE successfully (e.g. mastering the skills necessary) and enable self-regulation of action over time (e.g. providing prompts and cues to act, planning when, where, and how to perform TSSE). ASICA may enable earlier treatment and improved outcomes for patients and the National Health Service (NHS) by enabling prompt recognition and treatment of recurrent and new primary melanomas. The ASICA intervention was developed within the Medical Research Council (MRC) complex intervention framework [19] and includes BCTs selected to address constructs of the underpinning theories (information-motivation-behaviour (IMB)) model plus control theory and implementation intentions [20–25]. Development was guided by an expert multi-disciplinary group through several stages [18]. A systematic literature review was conducted, followed by interviews with potential recipients and a facilitated co-design event where all key stakeholders participated in the development of a prototype by acting out a full simulation: a tablet-based digital intervention to prompt and support TSSE, comprising instructional videos and electronic reporting (including photographs) to a clinical nurse specialist in dermatology with subsequent clinical triage [26].

The prototype was further developed in a preliminary 8-month feasibility study to establish its acceptability [18]. Nineteen people treated for melanoma stages 0-2C and who were receiving structured hospital-based follow-up were recruited from six general practices in North-east Scotland [18]. Users were prompted by email each month to undertake TSSE and provide electronic feedback of their findings to the clinical nurse specialist. Qualitative interviews were conducted with the participants after 8 months. Most participants were strongly positive and adhered well to the intervention (*n* = 15/19), and seven participants reported symptoms. Two underwent surgery as a result of participating; one with recurrent melanoma, the second with a benign compound naevus. Intention and confidence to conduct monthly TSSE increased. Issues to improve usability were identified and implemented. We concluded that ASICA is acceptable, safe and effective and offers potential to improve psychological well-being and enable earlier diagnosis of new primary and recurrent melanoma [18]. However, the non-randomised pre-pilot-study gave limited information on recruitment, acceptability, compliance and retention at one site. Also, we collected data on anxiety and depression, but not melanoma worry, and there was wide variability in the scores at baseline and variability in both the magnitude and direction of effect at follow-up, raising the possibility of a bi-directional effect on psychological outcomes that requires further exploration. This study aims to demonstrate that ASICA has the potential to benefit people with melanoma and is feasible to deliver in the NHS.

## Aims and objectives

The aim of the study is to compare a self-directed digital intervention (intervention group) with treatment as usual (control group) in patients treated for a first-stage 0-2C primary cutaneous melanoma within the preceding 60 months.

The hypothesis to be tested is that among patients with melanoma, the ASICA intervention will increase the practice of TSSE in those who use it, compared to controls, without affecting psychological well-being, and will lead to earlier detection of recurrent and new primary melanoma.

The specific study objectives are to:Recruit 240 adult patients with a previous first-stage 0-2C primary cutaneous melanoma.Randomise participants to the ASICA intervention or the control group.Collect baseline patient-reported and clinical data. The baseline participant questionnaire will include the modified Melanoma Worry Scale (MWS) the Hospital Anxiety and Depression Scale (HADs), the EuroQoL 5-dimension 5-level questionnaire (EQ-5D-5 L), and questions about TSSE practice, intentions, self-efficacy and planning.Follow up participants by postal questionnaire at 3, 6 and 12 months after randomisation. Shortened questionnaires (HADS, EuroQoL EQ-5D-5 L, and MWS) will be completed at 3 and 6 months and a full questionnaire, as per baseline, at 12 months.Compare the primary and secondary outcomes between the two arms.Collect data from the intervention group via tablet monitoring, for process evaluation to investigate the frequency and patterning of total skin examination and investigate predictors of sustained skin examination over time.

## Methods

### Study design

This is a two-arm, open multi-centre randomised controlled trial (RCT) comparing ASICA, a digital intervention to increase TSSE by people treated for melanoma, with usual follow up. The trial flow diagram is presented in Fig. 1. This protocol follows Standard Protocol Items: Recommendation for Interventional Trials (SPIRIT) guidelines [27]. Participants will be in the trial for 12 months. The primary outcome will be determined up to 12 months after randomisation.

**Fig. 1 Fig1:**
[figure not shown]
Flow diagram of study design and schedule. SAE, serious adverse event; ASICA, Achieving Self-directed Integrated Cancer Aftercare; HADS, Hospital Anxiety and Depression Scale; EQ-5D, Euroqol 5-dimensions questionnaire; NHS, National Health Service

### Study participants

#### Inclusion criteria

We will include adults (age 18 years and over) who have been treated within the preceding 60 months for a previous stage 0-2C primary cutaneous melanoma and can give informed consent.

#### Exclusion criteria

Exclusion criteria are stage 3 and 4 melanoma; previous local recurrence of melanoma within the last 60 months; inability to consent and/or complete questionnaires (e.g. due to cognitive or language issues) and blindness or visual impairment.

### Recruitment

A clinical nurse specialist in dermatology will work with lead clinicians at the two recruiting sites, Aberdeen Royal Infirmary and Addenbrooke’s Hospital, Cambridge. Potential participants will be identified from appropriate sources including, but not limited to, Multidisciplinary Team (MDT) meeting lists, locally held pathology registers and melanoma follow-up clinic registers. Following identification of potential participants, an invitation letter, patient information leaflet (PIL) detailing the trial, consent form, baseline questionnaire and pre-paid return envelope will be sent out directly from the treating hospital. Local contact details will be provided. Potential recruits will be offered the opportunity to meet face to face or have a telephone conversation with a member of the investigative team to discuss their potential participation. Local procedures at the participating hospitals are different and the timing and mode of approaching patients and the consent process may vary in order to accommodate both the specific circumstances at each site and the needs of the patients.

### Informed consent

Potential participants will have the opportunity to discuss all aspects of the proposed research with the local clinical team, family and friends and, if appropriate, with their General Practitioner (GP). Patients who decide to participate will send their completed documents (consent form and baseline questionnaire) in the pre-paid envelope provided to the local clinical team. Participants will be asked to consent to being randomised to receive ASICA or to the control group; to permit the research team to review their secondary-care medical notes at baseline and outcome; to receive the study questionnaires and for future contact to enable longer-term follow up of both groups.

### Randomisation and allocation

Participants will be randomised using a minimisation algorithm based on gender and centre, to minimise imbalance between the intervention and control groups [28]. All participants who enter the trial will be logged with the central study office in Aberdeen and given a unique study number. Participants will be randomised 1:1 control-to-intervention, using the validated remote automated computer randomisation application at the study administrative centre in the Centre for Healthcare Randomised Trials (CHaRT) in the Health Services Research Unit (HSRU), University of Aberdeen. This randomisation application will be available as an Internet-based service. The Principal Investigator (PI), or individual with delegated authority at the site, will access the Web-based system to randomise participants. Participants will be informed of their allocated treatment group after randomisation.

### The intervention that will be evaluated

The intervention will be evaluated as follows:Preparation and training: the intervention group will attend a local medical photography suite to have digital skin images taken. The ASICA intervention app and individual skin-maps will be incorporated within a password-protected individual tablet computer to ensure confidentiality. The app is Android-configured and designed to run on a Samsung Galaxy tablet. The ASICA app comprises (1) an instructional video demonstrating how to conduct a sequential TSSE; (2) a digital skin map of the patient’s own skin; (3) a digital camera and instructions about how to take photographs of skin lesions; (4) a structured electronic TSSE report form, which can be sent to a clinical nurse skin cancer specialist (CNS), which can include photographs of skin lesions that the patient is concerned about. All reports are managed within a secure encrypted server. Participants randomised to the ASICA intervention will be invited to receive their tablet computer at a 60-min group training session held at the local recruiting centre. At these sessions intervention group participants will be instructed how to use the tablet computer and ASICA app to guide themselves through TSSE and send the findings electronically to the study server. Participants will have the opportunity to familiarise themselves with their tablet for a short time before their first skin TSSE. All aspects of using the tablet, from ensuring the internet is connected, detailed step by step instruction, contact details, screen shots of the app to hints and tips on taking photographs with the tablet are contained in a booklet that will be issued to each participant.Prompting to use ASICA: the intervention group will be supported by a clinical nurse specialist in dermatology based in Aberdeen and each month they will be prompted (using the participant’s favoured method of contact (phone, email, text or mail) to conduct a TSSE.Performing and reporting TSSE using ASICA: participants will be asked to follow the TSSE procedure outlined in the integral animated ASICA demonstration and respond using the electronic report form. Where the participant finds a skin lesion that raises concern (either new or associated with their primary site) they will take photographs of the lesion using the camera on their tablet computer. Such photographs will be uploaded and attached to the digital report sent to the clinical nurse specialist.Response by the clinical nurse specialist: the digital reports will be sent to the clinical nurse specialist who will check and log them. The clinical nurse specialist will log all data on TSSE activity (check TSSE conducted, body areas (1–8) checked, concerns noted) and data will be exported into the database for process analysis.Action where the report causes concern: where a patient has registered a concern within their digital report about something they have found during TSSE, the clinical nurse specialist will observe this from the report and contact the patient within 72 working hours for further discussion. They will discuss concerns by telephone in the first instance. Clinical images will be reviewed and further images sent if required. Our pilot study suggests many concerns will be successfully resolved at this early stage.Further clinical action: where discussion and review of clinical images has not fully resolved the concerns of the patient and/or clinical nurse specialist, the clinical nurse specialist will discuss the case and review any clinical images with the site’s lead dermatologist, and an urgent clinic appointment will be arranged.

All participants (intervention and control) will continue to attend their usual structured melanoma follow up as determined by local guidelines throughout the trial. Usual structured melanoma follow up consists of regular (3-monthly or 6-monthly) review appointments with a specialist skin physician or nurse conducted at the secondary care hospital outpatient department. The schedule of appointments is determined by the clinical features of the participant’s primary melanoma.

### Follow-up procedures

Intervention and control group participants will receive postal questionnaires at 3, 6 and 12 months after randomisation. Reminders will be sent to non-responders after 3 weeks. The medical notes of all participants will be reviewed at 12 months and any relevant pathology data will be collected.

### Subsequent arrangements

The local Research Nurse and/or PI will:File a copy of the consent form in the hospital notes along with information about the study.Enter study data on the participant into the bespoke study database hosted by the CHaRT in the Health Services Research Unit, University of Aberdeen.Maintain study documentation at main research office. A copy of the signed consent form will be returned to the Trial Office in Aberdeen.Provide any relevant follow-up clinical data.

Participants will be asked for their preferred mode of contact to be prompted to conduct a monthly TSSE, by phone, post or email. In the case of non-return of questionnaires, attempts will be made by site staff or staff at the Trial Office to trace the participant directly using these means or indirectly by contacting the GP.

### Change of status/withdrawal procedures

Participants will remain in the trial unless they choose to withdraw consent or if they are unable to continue for a clinical reason. All changes in status with the exception of complete withdrawal of consent will mean the participant is still followed up for all trial outcomes wherever possible. All data collected up to the point of complete withdrawal will be retained (with permission) and used in the analysis. The study team will attempt to collect the tablet computer issued to the withdrawing participant.

### Outcome measures

#### Primary outcome

The co-primary outcome measures are the impact of ASICA on worry about melanoma (the Melanoma Worry Scale (MWS)), anxiety and depression (HADS) and quality of life (EQ-5D-5 L) 12 months after randomisation.

#### Secondary outcomes

Adherence to TSSE recommendations in the year following the introduction of ASICA.Detection of second primary and recurrent melanoma.Intention and self-efficacy and clearer plans to perform TSSE in the next 12 months. Intention, self-efficacy and plans will be measured using the baseline and outcome questionnaire measures.Pattern of NHS resource use.

### Data collection and processing

Follow up will continue for 12 months from the date of randomisation. Outcomes will be assessed by participant-completed questionnaires at baseline and 3, 6 and 12 months after randomisation. The research nurse and/or clinician will complete the case report form (CRF) at baseline and at 12 months after randomisation. The components and timing of follow-up measures are shown in Fig. 2 (SPIRIT Figure [27])

**Fig. 2 Fig2:**
[figure not shown]
Schedule for assessments/data collection (Standard Protocol Items: Recommendations for Interventional Trials (SPIRIT) [27]. mth, months; ASICA, Achieving Self-directed Integrated Cancer Aftercare; EQ-5D, Euroqol 5-dimensions questionnaire; HADS, Hospital Anxiety and Depression Scale; MWS, Melanoma Worry Scale; TSSE, total skin self-examination

### Baseline

A participant visit will not be required to collect baseline data as these will be obtained from participants’ hospital medical records and by postal questionnaire. Participants’ details (age, gender, ethnicity, habitation status, occupation, GP practice, date of melanoma diagnosis, clinical details about melanoma, important comorbidities) will be recorded in the electronic CRF. NHS resource use with respect to skin services will be collected for the 2 years preceding randomisation including number of melanoma follow-up appointments and grade of clinician seen; the number, type and duration of skin-related hospital admissions and the number of additional skin-related hospital outpatient attendances and the grade of physician seen. Participants will complete a questionnaire collecting data on quality of life (EQ-5D-5 L [29]), anxiety and depression (HADS [30]), worry about melanoma (MWS) [31]), self-report of health service use, self-report of TSSE practice (frequency and coverage) and ratings of intention, self-efficacy and planning for future TSSE [32].

### Follow up

Participants will be asked to complete a questionnaire, similar to the baseline questionnaire, to assess outcome measures at 12 months, with a shortened questionnaire at 3 and 6 months after randomisation. These questionnaires will be administered by post or email as preferred by the participant. The research nurse will also re-review participants’ medical records at outcome to collect data on skin-related NHS resource use during the study year, including details of any new skin-related diagnoses and details of melanoma follow-up appointments and other skin-related hospital attendances and admissions. The CRF will enable the clinical nurse specialist to collect relevant baseline and outcome data from secondary care case-notes (including pathology data).

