#### Additional data from the intervention group

Adherence to TSSE will be measured using reports of TSSE from the intervention group, which will provide information on the frequency and pattern over time of TSSE, maintenance throughout the 12 months, the time taken and the areas of the body covered. These data will be analysed to assess usage and predictors of usage of ASICA that might be useful in designing improvements to the procedures.

The research nurses will enter locally collected data at the trial centres. Serious adverse events and adverse events will be notified immediately to the PI and recorded by the Trial Office in Aberdeen. Staff in the Trial Office will work closely with the local Research Nurses to ensure the data are as complete and accurate as possible. Study questionnaires will be sent to participants from the Trial Office in Aberdeen and participants will return the completed questionnaires to the Trial Office. Extensive range and consistency checks will be used to further ensure the quality of the data.

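### The article assigns 12-month outcome and pathology extraction to more than one role, and one of them carries the title of the nurse who supports and triages the ASICA arm

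*Protocol article*

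**What the plan says.** The protocol article describes the 12-month review of case notes in several places:

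- **Follow-up procedures** names no one: "The medical notes of all participants will be reviewed at 12 months and any relevant pathology data will be collected".
- **Subsequent arrangements** has the local research nurse and/or PI enter study data and supply follow-up clinical data.
- **Data collection and processing**: "The research nurse and/or clinician will complete the case report form (CRF) at baseline and at 12 months after randomisation".
- **Follow up**, penultimate sentence but one on this subject: "The research nurse will also re-review" the medical records. The task there covers skin-related NHS resource use, new skin-related diagnoses, and appointments, attendances and admissions.
- **Follow up**, last sentence: "The CRF will enable the clinical nurse specialist to collect relevant baseline and outcome data from secondary care case-notes (including pathology data".
- On data entry, the section **Additional data from the intervention group** says: "The research nurses will enter locally collected data at the trial centres".

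The title clinical nurse specialist has a defined job in the section on the intervention: "the intervention group will be supported by a clinical nurse specialist in dermatology based in Aberdeen". This nurse checks and logs the digital reports. Where a participant registers a concern, "the clinical nurse specialist will observe this from the report and contact the patient within 72 working hours for further discussion". Unresolved cases are taken, with the images, to the site's lead dermatologist.

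Study design describes a "two-arm, open multi-centre randomised controlled trial (RCT"). Secondary outcomes include detection of second primary and recurrent melanoma and the pattern of NHS resource use. Under Statistical analysis, one-year detection of new primary, in-situ, dysplastic and recurrent lesions is tabulated by arm.

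**The concern.** Two things are wrong with the text as it stands. First, it does not settle who extracts the 12-month clinical outcomes. Second, one of the roles it names is the role that delivers part of the intervention.

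A nurse who has logged ASICA reports and reviewed lesion photographs would open an intervention participant's notes already knowing which lesions to look for. The article describes no equivalent source of information for controls. Some steps in extraction need judgement: whether a lesion is relevant, and whether it is a recurrence or a new primary. If such a nurse searched the notes more thoroughly in one arm, detection would be raised in the ASICA arm, which is the direction of the trial's hypothesis of earlier detection. Sample size says that recurrence and new-melanoma rates are quantified here ahead of a definitive trial powered on clinical outcomes, so an artefact could carry forward.

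**Working it through.** The article states no figure on this point, so the check compares the statements on who does what.

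1. **Is the assignment inconsistent?** Three descriptions of the extractor can be read from the article: research nurse (Follow up, first record-review sentence), research nurse and/or clinician (Data collection and processing), and clinical nurse specialist (Follow up, last sentence). Subsequent arrangements adds the PI as a possible supplier of follow-up clinical data, and Follow-up procedures is silent. The two Follow up sentences are adjacent and overlap in content: new skin-related diagnoses go to the research nurse, while outcome data including pathology go to the clinical nurse specialist. A detected melanoma falls under both. The inconsistency is confirmed.

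2. **Does the clinical nurse specialist deliver the intervention?** Yes, for the role described in the intervention section. Prompting, logging, telephone contact and escalation concern the intervention group only.

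3. **Is it the same nurse?** This is not stated. Follow up uses the same title with the definite article, which makes identity the natural reading. The intervention section places the supporting nurse in Aberdeen; Follow up does not say who would extract notes at Cambridge.

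4. **Which outcomes are exposed?**
   - Detection: yes, since pathology and outcome data are named in the disputed sentence.
   - Resource use: mostly no. It is given expressly to the research nurse and is also self-reported in the questionnaires. Only the broad reference to outcome data overlaps.
   - Melanoma worry, HADS and EQ-5D-5L: no. Participants complete them and return them to the Trial Office.

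5. **Does a stated safeguard cover it?** The design is open and the article describes no masked extraction or classification. The range and consistency checks under Additional data from the intervention group act on values that were entered; they would not reveal a lesion that was never entered.

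6. **Can the size be derived?** No. The article gives neither a rate of missed lesions in notes review nor any measure of agreement between extractors.

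**The case against.** The strongest reply is that this is loose naming of roles. Most of the text points to local research staff; the disputed sentence says only what the form will enable; and the word clinician in Data collection and processing could include a specialist nurse. Notes and pathology are collected for all participants in both arms, and transcribing histology is fairly objective. Detection is a secondary outcome that is tabulated in a pilot expressly not powered for clinical differences. Much of this stands and is why the severity is limited. It does not remove the need to correct a sentence that, followed as written, gives outcome extraction to a role tied to one arm.

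A reader might infer more than the document supports:

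- *That one nurse knows every ASICA lesion and no control lesion.* Identity of the two nurses is inferred. Recruitment has a dermatology clinical nurse specialist working with lead clinicians at both sites, and both arms stay in specialist or nurse follow-up, so such a nurse may know control lesions too.
- *That resource use is equally exposed.* The research nurse is named for that task.
- *That a higher count in the ASICA arm would show bias.* More detection there is also the intended effect of the intervention.
- *That the distortion can be quantified.* One could treat the Background figures (about 20% recurrence, 4–8% new primary) as 5-year risks: (20% + 4%)/5 = 4.8% and (20% + 8%)/5 = 5.6% a year, or 120 × 0.048 = 5.8 to 120 × 0.056 = 6.7 events per arm. Two extra lesions in one arm would then turn 6 v 6 into 8 v 6, a ratio of 8/6 = 1.33. But the article gives no time horizon for those percentages, the division assumes a constant rate and no overlap, dysplastic lesions are left out, and the two extra lesions are invented.
- *That switching to a research nurse removes the risk.* Site staff carry out randomisation in an open trial, so a research nurse may also know the allocation.

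**Conclusion.** The concern holds as an inconsistency with a plausible consequence. The article names different extractors for the same 12-month data, and on the natural reading one of them helps deliver ASICA. That leaves the detection outcome open to more complete ascertainment in the intervention arm. Nothing in the document shows that this would happen, and no size can be attached to it.

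The conclusion rests on one assumption: that the clinical nurse specialist in Follow up is the one in the intervention section. If they are different people and the extractor has no ASICA role, what remains is a wording conflict to tidy up. Severity is minor to moderate: one secondary outcome is affected, the risk is least where a lesion is histologically confirmed, and the co-primary outcomes are unaffected.

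**What to change.** Amend the last sentence of Follow up so that the site research nurse already named, with no role in delivering or triaging ASICA, extracts 12-month outcome and pathology data for both arms on the same structured CRF. Bring Follow-up procedures, Subsequent arrangements, Data collection and processing, and Additional data from the intervention group into line. Limit the clinical nurse specialist's contribution to the ASICA usage log.

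Where existing staff allow, have lesions classified from pathology reports with allocation removed. Otherwise, report unmasked extraction as a limitation when detection is tabulated by arm.

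The change needs no new post, visit or participant. Its cost is some added coordination for the research nurse. It takes away the extractor's arm-specific knowledge gained from ASICA reports; it does not by itself mask allocation, which is why the pathology step or the stated limitation is needed as well.
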